### Participants and recruitment

Eighty patients aged 26–55 years with an HbA1c level >70 mmol/mol at the time of enrolment will be included. Exclusion criteria to the study will be ongoing severe depression, eating disorders or other severe mental illnesses, alcohol or substance abuse, or severe diabetes complications. Oral and written information about the present study will be given to patients who fulfil the inclusion criteria. Written informed consent or assent for participation in the study will be obtained from the participants.

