### Randomisation

Participants who fulfil the inclusion criteria and are willing to participate in the study and have completed the pre-test will be randomly allocated to either the intervention or wait-list control group. A flow chart of the study is shown in Additional file 1.

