### Statistical analysis and power calculation

To detect a difference of 6 mmol/mol in HbA1c (SD ± 11) at least 35 participants are needed in each group (power 80 % and alfa 0.05). In view of the drop-off, 80 patients will be included. The differences between the groups will be analysed with unpaired t-tests with 95 % confidence intervals and *p* < 0.05 considered as significant. Repeated- measures analysis of variance will be used for comparisons in the groups in pre- and post-measuring with the same confidence interval and level of significance. When testing differences between groups regarding AAQ2 and ‘Check your health’, the same statistical analysis will be used.

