## Discussion

The aim of this study is to test the effects of an ACT group treatment and its effect on glycaemic control and well-being. ACT is a modern psychological intervention.

Previous studies have reported good preliminary results for ACT in numerous behavioural medicine areas [13, 28–30].

We have chosen to include patients with higher HbA1c values (above 70 mmol/mol) because we want to see if the participants using the tools they receive from ACT treatment can lower their HbA1c level and also experience improved well-being. To detect changes in perceived physical health, general QoL and the burden of diabetes, we will use the HADS, *‘*Check your health’ scale and AAQ2. The intervention will take 7 weeks and perceived QoL will be evaluated at baseline, 6 and 12 months to allow comparisons and to determine any changes.

Sweden has a national register that includes 90 % of all patients. Data from this register show that HbA1c level is increasing every year for patients with type 1 diabetes [31]. This finding highlights the need to take strong measures to help patients achieve optimal glycemic control while maintaining a good QoL, especially as good glycaemic control prevents or postpones complications.

The prevalence of depression is overrepresented in patients with diabetes, which indicates the need for psychological support. Psychiatric co-morbidity is associated with poorer glycaemic control among patients with diabetes [7]. Diabetes is a disease in which self-care is ongoing; therefore, the patient is the most important partner in the team, in collaboration with nurses and clinicians, including a psychologist. A psychologist and diabetes specialist nurse will lead this ACT study.

In a study with similar ambitions to this study, patients with type 2 diabetes had a 1- day training workshop with ACT [22]. After 3 months, these patients were more likely to use these coping strategies, reported better diabetes self-care and had HbA1c values within the target range No studies have been conducted in participants with type 1 diabetes. Thus, there is a lack of evidence in the field, and the intent of this study is to address this gap.

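### Within-arm pre/post tests of HbA1c are biased toward a fall by the entry threshold above 70 mmol/mol if the qualifying value is also the baseline, so they cannot support a treatment claim

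*Protocol article*

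**What the plan says.** The Protocol article, section *Statistical analysis and power calculation*, names two procedures. First: "The differences between the groups will be analysed with unpaired t-tests". Second, repeated-measures "analysis of variance will be used for comparisons in the groups in pre- and post-measuring", with the confidence interval and significance level of the first. Neither is ranked above the other, and the second is not labelled descriptive.

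Under *Participants and recruitment*, patients "with an HbA1c level >70 mmol/mol at the time of enrolment will be included". The *Discussion* gives the reason for the threshold: "we want to see if the participants using the tools they receive from ACT treatment can lower their HbA1c level".

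Under *Randomisation*, participants who have completed a pre-test are "randomly allocated to either the intervention or wait-list control group". *Measures and data collection* has HbA1c taken before treatment starts and again at 6 and 12 months. Nothing says whether the pre-treatment HbA1c is the value that qualified the patient or a fresh measurement.

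**The concern.** A patient selected for a high reading of a variable measured with error and natural fluctuation will, on average, read lower next time. Both arms are selected this way, so both are expected to fall without any treatment effect. A within-arm test at 0.05 has zero change as its null hypothesis, which is the wrong reference here: it can reject because of how patients were chosen.

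Two results would then be easy to misread: a significant fall in the treated arm, and a significant fall in the treated arm with none in the wait-list arm. Neither compares the arms. Because the plan gives the within-arm test the same significance level as the randomised comparison, a report could cite it as support even if the between-group difference were not significant.

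**Working it through.** **The plan's own figures.** It powers for a difference of 6 mmol/mol with SD 11, 80% power and alpha 0.05, and states 35 per group. The usual two-sided formula gives 2 × (1.960 + 0.842)² × 11² / 6² = 52.8, so 53 per group. The stated 35 is not reproduced. That is a separate matter; here 35 serves only as the arm size and 6 mmol/mol only as a yardstick.

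**Inputs.** From the document: threshold 70 mmol/mol, n = 35 per arm, two-sided 0.05 (implied by the 95% intervals). Assumed, because the document gives none of them: mean m of the clinic population 60 to 66, its SD s 11 to 15, test-retest correlation r 0.7 to 0.9. Also assumed: a normal distribution, no treatment effect, no drift, and the qualifying value used as baseline.

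**Step 1, expected fall.** With z = (70 − m)/s and λ = φ(z)/(1 − Φ(z)), the expected fall is s(1 − r)λ. For m = 63, s = 13, r = 0.8: z = 0.538, λ = 0.345/0.295 = 1.169, fall = 13 × 0.2 × 1.169 = 3.04 mmol/mol.

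**Step 2, SD of the change.** Among selected patients this is s × √[(1 − r)²(1 + zλ − λ²) + (1 − r²)]. In the same case: 13 × √(0.04 × 0.262 + 0.36) = 7.91. The standard error is 7.91/√35 = 1.34, so the fall is about 2.3 standard errors, against a critical value of 2.03 on 34 degrees of freedom.

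**Step 3, how often the arm is falsely significant.** Simulated paired t-test, counting falls only (nominal rate 2.5%):

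| m, s, r | λ | Fall (mmol/mol) | SD of change | Fall / SE | Falsely significant |
|---|---|---|---|---|---|
| 66, 11, 0.9 (smallest fall) | 1.043 | 1.15 | 4.83 | 1.4 | 27–28% |
| 63, 13, 0.8 | 1.169 | 3.04 | 7.91 | 2.3 | 60% |
| 60, 15, 0.7 (largest fall) | 1.265 | 5.69 | 10.94 | 3.1 | 84–85% |

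The largest fall does not give the highest rate, because the SD grows with it. Over all combinations in these ranges the rate runs from about 25% (66, 15, 0.9) to 93% (60, 11, 0.7).

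**Step 4, the between-group test.** In simulations over a wider grid (m 60 to 68, s 11 to 14, r 0.6 to 0.95), and in runs with drift added, the unpaired t-test on follow-up HbA1c rejected in 4.4% to 5.8% of trials. Over the same wider grid without drift, one named arm was significant and the other not in about 2% to 26% of trials, although neither had an effect.

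**Step 5, what shrinks the bias.**
- Upward drift: the *Discussion* reports that register HbA1c in type 1 diabetes rises each year, without giving a size. At m = 64, s = 11, r = 0.8 the false rate is 61% with no drift. An assumed rise of 2 mmol/mol brings it to 7% (27% at r = 0.7, 0.3% at r = 0.9).
- A separate pre-test: if baseline is a fresh measurement and the fluctuation is transient, the rate returns to 2.5–2.9%.

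**The case against.** The strongest reply is that the plan already contains the valid comparison and states it first. The trial is randomised against a wait-list, the sample size is for a between-group difference, and nowhere does the document say that a treatment claim will rest on the pre/post test. This stands: a reader might infer that the trial's conclusion depends on an uncontrolled comparison, and the text does not support that. What remains is that a biased test is planned at the same significance level with nothing to say that it is only descriptive.

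The ANOVA sentence is also ambiguous. It could mean a model with group and time, and the sentence after it, on between-group differences in two questionnaires, refers back to the same analysis. A group-by-time term would escape the criticism. But the contrast between comparing groups and comparing within them makes the within-arm reading the natural one.

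A reader might infer that the arms are bound to show an improvement. That is too strong: the result depends on undocumented inputs, on whether the pre-test is separate, and on the rising trend that the document cites. None of this rescues the test, because its error rate then depends on opposing biases of unknown size.

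A reader might also take the *Discussion* sentence about participants lowering their HbA1c as a commitment to within-arm inference. It is a rationale for eligibility, not an analysis rule.

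Finally, HADS, AAQ2 and Check your health have no score threshold for entry, so the argument does not carry over to them directly.

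**Conclusion.** The point holds for HbA1c and in limited form. On its natural reading, the plan includes a within-arm test that selection above 70 mmol/mol biases toward a fall if the qualifying value is the baseline. Under the assumed inputs the artefact is about 1 to 6 mmol/mol, which is not small beside the planned difference of 6. It is falsely significant in roughly 28% (smallest fall) to 84% (largest fall) of arms of 35. Upward drift or a separate pre-test could reduce this to little or nothing. Neither a significant fall in the treated arm nor significance in one arm only can support a treatment claim. The randomised between-group comparison is sound in this respect.

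**What to change.** - State that the effect on HbA1c is judged only on the between-group contrast: follow-up HbA1c adjusted for baseline (ANCOVA), or the group-by-time term of the repeated-measures model.
- Report within-arm HbA1c changes descriptively, as means with 95% confidence intervals, and draw no conclusion on efficacy from them.
- Say whether the pre-test HbA1c is separate from the qualifying value. If it is, use the pre-test as baseline.

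The cost is analysis wording only. Baseline HbA1c is already collected, and no patients, visits or measurements are added. What is given up is a set of within-arm HbA1c p-values that are not valid evidence of a treatment effect.

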### Ethical considerations

The ethical review board in Uppsala, Sweden, has approved the study (2014/301).

## Discussion

The aim of this study is to test the effects of an ACT group treatment and its effect on glycaemic control and well-being. ACT is a modern psychological intervention.

Previous studies have reported good preliminary results for ACT in numerous behavioural medicine areas [13, 28–30].

We have chosen to include patients with higher HbA1c values (above 70 mmol/mol) because we want to see if the participants using the tools they receive from ACT treatment can lower their HbA1c level and also experience improved well-being. To detect changes in perceived physical health, general QoL and the burden of diabetes, we will use the HADS, *‘*Check your health’ scale and AAQ2. The intervention will take 7 weeks and perceived QoL will be evaluated at baseline, 6 and 12 months to allow comparisons and to determine any changes.

Sweden has a national register that includes 90 % of all patients. Data from this register show that HbA1c level is increasing every year for patients with type 1 diabetes [31]. This finding highlights the need to take strong measures to help patients achieve optimal glycemic control while maintaining a good QoL, especially as good glycaemic control prevents or postpones complications.

The prevalence of depression is overrepresented in patients with diabetes, which indicates the need for psychological support. Psychiatric co-morbidity is associated with poorer glycaemic control among patients with diabetes [7]. Diabetes is a disease in which self-care is ongoing; therefore, the patient is the most important partner in the team, in collaboration with nurses and clinicians, including a psychologist. A psychologist and diabetes specialist nurse will lead this ACT study.

In a study with similar ambitions to this study, patients with type 2 diabetes had a 1- day training workshop with ACT [22]. After 3 months, these patients were more likely to use these coping strategies, reported better diabetes self-care and had HbA1c values within the target range No studies have been conducted in participants with type 1 diabetes. Thus, there is a lack of evidence in the field, and the intent of this study is to address this gap.
